## Abstract

**Introduction:**

Xin-Li-Fang (XLF), a representative Chinese patent medicine, was derived from years of clinical experience by academician [name], and is widely used to treat chronic heart failure (CHF). However, there remains a lack of high-quality evidence to support clinical decision-making. Therefore, we designed a randomized controlled trial (RCT) to evaluate the efficacy and safety of XLF for CHF.

**Methods and design:**

This multicenter, double-blinded RCT will be conducted in China. 300 eligible participants will be randomly assigned to either an XLF group or a control group at a 1:1 ratio. Participants in the XLF group will receive XLF granules plus routine care, while those in the control group will receive placebo granules plus routine care. The study period is 26 weeks, including a 2-week run-in period, a 12-week treatment period, and a 12-week follow-up. The primary outcome is the proportion of patients whose serum NT-proBNP decreased by more than 30%. The secondary outcomes include quality of life, the NYHA classification evaluation, 6-min walking test, TCM symptom evaluations, echocardiography parameters, and clinical events (including hospitalization for worsening heart failure, all-cause death, and other major cardiovascular events).

**Discussion:**

The results of the study are expected to provide evidence of high methodological and reporting quality on the efficacy and safety of XLF for CHF.

**Clinical trial registration:**

Chinese Clinical Trial Registration Center (www.chictr.org.cn). The trial was registered on 13 April 2022 (ChiCTR2200058649).

## 1. Introduction

Chronic Heart Failure (CHF) is a clinical syndrome of abnormal cardiac structure and/or function with various causes. It leads to the decline of cardiac output, systolic and/or diastolic dysfunction, metabolic derangements, and myocardial cell death (1). In China, 1.5–3.5% of the population suffers from heart failure (2). However, with the development of modern medicine, the HF survival rate is gradually rising, while the morbidity, mortality and hospitalization rates caused by HF have either remain unchanged or worsened (2).

Traditional Chinese medicine (TCM) has immense potential in improving cardiac systolic and diastolic function, patient quality of life, and other factors, and can be considered a supplementary and alternative therapeutic strategy for CHF treatment (3). Through the analysis of TCM syndrome and medication rules for CHF, it has been shown that a syndrome called Qi deficiency and Blood stasis and Water-Dampness retention (QBWD) is the most common syndrome for patients with heart failure, throughout the entire course of the disease (4, 5).

Xin-Li-Fang (XLF), as a representative Chinese patent medicine, is derived from years of clinical experience from academician [name], and is widely used to treat the CHF associated with QBWD syndrome. Details on XLF are listed in Table 1. XLF is composed of *Plantaginis Herba* (Che Qian Cao), *Curcumae Rhizoma* (E Zhu), *Ginseng Radix Et Rhizoma Rubra* (Hong Shen), *Astragali Radix* (Huang Qi), *Astragali Radix Praeparata Cum Melle* (Zhi Huang Qi) and *Corni Fructus* (Shan Zhu Yu).

**Table 1 T1:** Components of Xin-Li-Fang.

**No**.	**Chinese name/*pinyin***	**Latin scientific name/scientific name**	**Part and form used**	**Place of origin (China)**
1	车前草/ Che Qian Cao	*Plantaginis Herba/ Plantago asiatica L*.	Dried whole grass	Anhui
2	莪术/ E Zhu	*Curcumae Rhizoma/ Curcuma kwangsiensis S. G. Lee et C. F. Liang*	Dried rhizome	Guangxi
3	红参/ Hong Shen	*Ginseng Radix Et Rhizoma Rubra/ Panax ginseng C. A. Mey*.	Dried root and rhizome	Dongbei
4	黄芪/ Huang Qi	*Astragali Radix/ Astragalus membranaceus (Fisch.) Bge.var.mongholicus (Bge.) Hsiao*	Dried root	Gansu
5	炙黄芪 Zhi Huang Qi	*Astragali Radix Praeparata Cum Melle/ Astragalus membranaceus (Fisch.) Bge.var.mongholicus (Bge.) Hsiao*	Dried root	Gansu
6	山茱萸/ Shan Zhu Yu	*Corni Fructus/ Cornus officinalis Sieb. et Zucc*.	Dried and ripe pulp	Henan

Our research team's previous studies have shown that in a rat model of CHF, XLF can improve heart function and increase the proportion of regulatory T (Treg) cells in the spleen and the lymph (this research has not been published). Meanwhile, it can also reduce the level of serum inflammatory factors and inflammatory body-related proteins, down-regulate the expression of Treg-related pathway proteins in myocardial tissue, decrease the proportion of ventricular fibrosis area, and play the role of anti-myocardial fibrosis in CHF rats (this research has also not been published).

However, there is still a lack of high-quality clinical evidence with endpoint events and adverse reactions as evaluation indexes, and the efficacy and safety of XLF remains unclear. Therefore, we designed a multicenter, double-blind, randomized placebo-controlled trial to investigate the effect and safety of XLF for CHF.

## 2. Methods

### 2.1. Design and settings

This study is a multicenter, randomized, double-blind, placebo-controlled clinical trial in which patients will be recruited from the outpatient cardiology departments at seven centers in China. The sites include Guangdong Provincial Hospital of Chinese Medicine, Xiyuan Hospital of CACMS, First Teaching Hospital of Tianjin University of Traditional Chinese Medicine, Shuguang Hospital of Shanghai University of Traditional Chinese Medicine, The Affiliated Hospital of Shandong University of Traditional Chinese Medicine, The First Affiliated Hospital of Henan University of Chinese Medicine and Xinjiang Uygur Autonomous Region Hospital of Traditional Chinese Medicine. Eligible participants with CHF will be randomly assigned to receive either XLF or a placebo for 12 weeks, and then will be followed for 12 weeks.

Figure 1 is a flowchart of the study design. The trial has been approved by the Ethics Committee at Guangdong Provincial Hospital of Chinese Medicine (BF2021-261-01) and registered with an identifier (ChiCTR2200058649) in the Chinese Clinical Trial Registry. Additionally, a Standard Protocol Items: Recommendations for Interventional Trials (SPIRIT) figure for the schedule of enrolment, interventions, and assessments is presented in Table 2.

**Figure 1 F1:**
[figure not shown]
Study flowchart. CHF, chronic heart failure.

**Table 2 T2:** Study procedure table.

**Study phase time**	**Baseline**	**Intervention period**			**Follow-up**
	**−2 ~0 wks**	**4 wks**	**8 wks**	**12 wks**	**24 wks**
**Data collection at baseline**					
Inclusion/exclusion criteria	**√**				
Informed consent	**√**				
Demographic data	**√**				
Random number	**√**				
Medical history	**√**				
**Outcome measurements**					
NT-proBNP	**√**			**√**	
Echocardiography	**√**			**√**	
NYHA class	**√**	**√**	**√**	**√**	**√**
6MWT	**√**	**√**	**√**	**√**	
MLHFQ score	**√**	**√**	**√**	**√**	**√**
TCM symptom scores	**√**	**√**	**√**	**√**	**√**
Clinical-endpoint events	**√**	**√**	**√**	**√**	**√**
**Safety evaluation**					
Vital signs	**√**			**√**	
Physical examination	**√**			**√**	
Blood routine	**√**			**√**	
Urine routine	**√**			**√**	
ECG	**√**			**√**	
Blood biochemistry	**√**			**√**	
Chest radiograph	**√**			**√**	
**Other data**					
Biological sample	**√**			**√**	
Combined medications	**√**	**√**	**√**	**√**	**√**
Dispense drug	**√**	**√**	**√**		
Recovery drug		**√**	**√**	**√**	
Record AEs		**√**	**√**	**√**	**√**
Complications		**√**	**√**	**√**	
Compliance		**√**	**√**	**√**	**√**

NYHA, New York Heart Association; 6MWT, 6-min walk distance test; MLHFQ, Minnesota Living with Heart Failure Questionnaire; TCM, traditional Chinese Medicine; ECG, electrocardiogram; AE, adverse event.

“√” Represents the need for implementation at this point in time.

### 2.2. Participants

#### 2.2.1. Diagnostic criteria for CHF

(1) The CHF diagnostic criteria are based on the 2018 Chinese Guidelines for the Diagnosis and Treatment of Chronic Heart Failure published by the Chinese Medical Association Cardiovascular Disease Branch (6), 2021 ESC Guidelines for the diagnosis and treatment of acute and chronic heart failure (7), and the 2022 AHA/ACC/HFSA Guidelines for the Management of Heart Failure (8).

(2) Patients must have a history of CHF of at least 3 months, or clinical symptoms of HF for at least 3 months.

(3) Patients must have received standard medical treatment for at least 2 weeks and no modification of dosage or intravenous administration.

#### 2.2.2. Diagnostic criteria for “Qi deficiency and Blood stasis and Water-Dampness retention (QBWD)” syndrome

QBWD syndrome diagnosis refers to expert consensus on CHF diagnosis and treatment in Chinese medicine, and textbooks on internal medicine for integrated traditional Chinese and Western medicine (9, 10). Syndrome differentiation will be independently determined by two qualified TCM cardiologists according to the diagnostic criteria for TCM differentiation (Table 3).

**Table 3 T3:** Diagnostic criteria for traditional Chinese medicine syndromes.

**Qi deficiency and blood stasis and water-dampness retention (QBWD)**	
Main symptoms	1. Shortness of breath
	2. Weakness
	3. Palpitations
Qi deficiency syndrome	1. Palpitations and shortness of breath
	2. Fatigue
	3. Spontaneous sweating
	4. Pale complexion
	5. Pale tongue
	6. Corpulent tender tongue with indentations in the margin of the tongue
	7. Weak pulse
	The included patients need to have two or more of the above symptoms
Blood stasis syndrome	1. Dark purple lips, face or hands
	2. Purple, dark or bruised tongue
	3. Enlarged sublingual venation
	4. Uneven pulse
	The included patients need to have two or more of the above symptoms
Water-dampness retention syndrome	1. Edema
	2. Hydrothorax/Ascites
	3. Poor urination
	The included patients need to have two or more of the above symptoms

#### 2.2.3. Inclusion criteria

Patients who meet all of the following criteria will be enrolled:

At least 18 years of ageMeet the CHF diagnosis criteriaQBWD syndrome diagnosisNew York Heart Association (NYHA) classification stages II-IVSerum NT-proBNP≥450 pg/ml (11)Signed informed consent.

#### 2.2.4. Exclusion criteria

Patients with one of the following conditions will be excluded:

(1) CHF caused by any of the following conditions: valvular disease, congenital heart disease, pericardial disease, cardiac arrhythmia, or other non-cardiogenic factors, including dysfunction in the kidneys, liver or lungs.

(2) Severe liver, kidney, hematological disease or abnormal renal or hepatic function. Patients with tumors, severe neural, endocrine or psychological disease; judgment from an investigator predicting that the survival period will not exceed 1 year.

(3) Comorbid with left ventricular outflow tract obstruction, myocarditis, hypertrophic cardiomyopathy, restrictive cardiomyopathy, aortic aneurysm, aortic dissection, congenital heart disease, or significant hemodynamic changes in patients with silent valvular heart disease; patients with cardiogenic shock, uncontrollable malignant arrhythmia, sinus or atrioventricular block without pacemaker treatment, progressive unstable angina pectoris or acute myocardial infarction.

(4) Patients undergoing cardiac resynchronization therapy, or who will undergo coronary revascularization or cardiac resynchronization therapy within 12 weeks.

(5) Patients with hypertension without control, SBP ≥ 180 mmHg and/or DBP ≥ 110 mmHg; SBP < 90 mmHg and/or DBP < 60 mmHg.

(6) Patients with allergies, or those who are known to be allergic to this medicine and its ingredients.

(7) Patients who have been involved in any clinical trial within the past month.

(8) Pregnant or lactating women.

(9) Investigator judges that patient could not complete the study or could not comply with the requirements of the study.

### 2.3. Recruitment process

Participants will be recruited *via* on-site screening of outpatients and inpatients, regular screening of potential participants using electronic medical records, and referrals from physicians and other providers. Patients who meet the inclusion criteria and sign informed consent forms will enter the screening period; otherwise, they will be excluded before randomization. Patients who agree to participate will be examined and diagnosed jointly by the main investigator and their attending physician according to the inclusion and exclusion criteria to determine their eligibility for the trial. Patients who pass the screening and sign the informed consent will be enrolled in the online allocation system and subsequently participate in the experiment's intervention and follow-up periods. In addition, the demographic characteristics of any ineligible patients and the reasons for not participating will be recorded. All personal patient information will be kept strictly confidential.

### 2.4. Randomization and allocation concealment

Through the central randomization system, the patients will be randomly divided into a Xin-Li-Fang group and a placebo group at a 1:1 ratio. Stratified by the central stratification method, we will use SAS 9.2 statistical software to generate random numbers and the random assignment results. The investigators will obtain the randomized number and drug number by a sequential number in the central randomization system. All center numbers, sequence numbers, randomization numbers, and drug numbers will be managed by the statistical unit.

### 2.5. Blinding

This study is a double-blind trial, in which neither participants nor study personnel will know the group allocation or be able to identify the treatment. Both the XLF and placebo granules will be manufactured by the Jiangyin Tianjiang Pharmaceutical Co., Ltd. (Jiangyin, China), and the placebo will be identical to the SGR in color, size, shape, and taste. All of the above drugs comply with the requirements of the National Drug Manufacturing Code of China. Blinding codes will be assigned after the randomization operation. This process will be operated by a specially assigned person, and the sequence number of the subject, corresponding random numbers and grouping results (i.e., the subjects are assigned to either a Group A or a Group B) will be the primary blinding base. Then, the two groups will be blinded to the medication, which will be the secondary blinding base (i.e., which of Group A or Group B used the TCM and which used the placebo), and each subject's drug number will be randomly prepared in order. All operations will be recorded and properly stored. The statistician will uncover the blinding when necessary, in case any serious adverse events (SAEs) occur during the course of the study, or emergency care is needed in an emergency situation. Once unblinded, the participant will be withdrawn from the study and the investigator will report the reason to the examiner within 24 h.

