#### 2.7.2. Secondary outcomes

The secondary outcomes will include: (1) Minnesota Living with Heart Failure questionnaire (12); (2) NYHA classification evaluation (13); (3) 6-min walking test (14); (4) TCM symptoms evaluation; (5) the Evaluation Scale of Dampness Syndrome of Traditional Chinese Medicine (15); (6) echocardiography parameters, and (7) clinical events (e.g., hospitalization for worsening heart failure, all-cause death, other major cardiovascular events).

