### 2.8. Safety assessments

Information on adverse events (AEs), including the occurrence time, severity, duration, adopted measures, and prognosis, will be recorded truthfully and in detail. Additionally, the investigator will assess every AE recorded to analyze the causality between the AE and the studied drugs. Serious adverse events (SAEs) are defined as events which can cause hospitalization, loss of ability to work, disability, congenital deformity, or death, according to the International Council for Harmonization of Technical Requirements for Pharmaceuticals for Human Use (ICH) guidelines (16). Besides the abovementioned measures, in the incidence of any SAE, the principal investigator will be notified. Additionally, a report will be submitted to the ethics committee and the data and safety monitoring committee (DSMC) within 24 h.

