### 2.13. Ethical considerations

This trial will be conducted in accordance with the principles of good clinical practice and the Declaration of Helsinki. Before signing informed consent, all participants will be informed of the purpose, interventions, possible benefits and harm of this study. Completing the informed consent form and qualifying for the trial will not affect patients' subsequent treatment, regardless of when or why they withdraw.

Patients will have the right to withdraw from the study at any time for any reason, but should try to avoid unnecessary withdrawal. They should take measures to complete follow-up as far as possible, so that its efficacy and safety can be evaluated. However, if a patient decides to withdraw, the researcher must contact the patient or his responsible relatives by telephone or personal interview, and confirm the reason for withdrawal if possible. The researcher will retrieve the remaining drugs when the patient withdraws, and complete the final evaluation and the case report as much as possible, explain the reason for withdrawal, and follow up on the occurrence of the endpoint event for the withdrawing patient. If the reason for patient withdrawal is an adverse event, this must be recorded in the complete CRF.

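### Section 2.5 withdraws unblinded participants from the study, which puts the only post-baseline NT-proBNP at outcome-related risk and is not reconciled with the withdrawal text in section 2.13

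*Protocol article*

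**What the plan says.** **Unblinding (section 2.5).** The first trigger is: "The statistician will uncover the blinding when necessary, in case any serious adverse events (SAEs) occur during the course of the study". A need for urgent care is the second. The consequence is: "Once unblinded, the participant will be withdrawn from the study".

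**Serious adverse events (section 2.8).** These are "events which can cause hospitalization, loss of ability to work, disability, congenital deformity, or death".

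**Clinical events (section 2.7.2).** The secondary outcomes include "hospitalization for worsening heart failure, all-cause death, other major cardiovascular events".

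**Primary outcome (section 2.7.1 and Table 2).** Response is a fall in NT-proBNP of more than 30% at week 12. Table 2 schedules NT-proBNP at baseline and week 12 only. Clinical events and adverse events are scheduled to week 24.

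**Withdrawal (section 2.13).** For a patient who chooses to leave, the researcher retrieves the remaining drug, completes a final evaluation as far as feasible, and will "follow up on the occurrence of the endpoint event for the withdrawing patient". An adverse event is recognised as a possible reason. Withdrawal imposed after unblinding is not mentioned.

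**Analysis (section 2.10).** Efficacy follows the intention-to-treat principle. The full analysis set leaves out participants who were wrongly enrolled, or who had no assigned treatment or follow-up. Unblinding is not a reason for exclusion.

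**The concern.** The rule in section 2.5 makes staying in the study depend on an event that may itself be an outcome. A participant admitted for worsening heart failure has had both a serious adverse event and a secondary efficacy event. If the blind is then broken, the text takes that participant out of the study.

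Before week 12 this matters for the primary outcome, because no interim NT-proBNP is scheduled from which response could be judged. The participant would stay in the full analysis set without a measured outcome, and the reason for the gap would plausibly relate to prognosis. An analysis plan can say how to handle a missing value, but it cannot recover one that the protocol stopped collecting.

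For events up to week 24, sites have two texts. One says that the participant leaves the study. The other says that endpoint events are still followed, but it addresses a different kind of withdrawal. Sites could reasonably act in different ways.

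**Working it through.** **1. The passages side by side**

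| Question | Section 2.5 | Section 2.13 |
|---|---|---|
| Who is covered? | Anyone unblinded | Patients who choose to leave |
| What ends? | Participation in the study | Study drug (remainder retrieved) |
| Endpoint events afterwards? | Not stated | Followed |
| Week-12 NT-proBNP? | Not stated | Not secured; a final evaluation is attempted at withdrawal |

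An evaluation at, say, week 5 is not a week-12 value, so section 2.13 would not protect the primary outcome even if it were applied to unblinded participants.

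**2. The plan's own sample size (section 2.9)**

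Inputs: control 31.98%, XLF 50%, α = 0.05 (two-sided assumed), power 80%. Unpooled formula:

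n = [0.3198 × 0.6802 + 0.50 × 0.50] × (1.960 + 0.842)² / 0.1802² = 0.4675 × 7.849 / 0.03247 = 113.01, rounded up to 114.

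This reproduces the stated 114. The pooled version gives 116. The planned 150 per arm less 20% leaves 120, with power 81.4%.

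**3. Illustration of the bias**

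The article gives no rate of serious adverse events or of unblinding. Assume that a share w of an arm is unblinded and withdrawn before week 12, that all of them are non-responders, that the analysis is complete-case, and that other missed visits are unrelated to outcome. The observed response rate is then p / (1 − w).

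*No true effect (31.98% in both arms).* The spurious difference is p(w₁ − w₀) / [(1 − w₀)(1 − w₁)].

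- 5% against 2%: 0.3198 × 0.03 / (0.98 × 0.95) = 1.0 points.
- 10% against 5%: 0.3198 × 0.05 / (0.95 × 0.90) = 1.9 points.
- Equal withdrawal: zero.

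The sign favours the arm with more withdrawals. For scale, the standard error of the difference with 120 per arm is √(2 × 0.3198 × 0.6802 / 120) = 6.0 points.

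*Planned effect (18.02 points).*

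| Withdrawn, XLF / control | Observed difference (points) |
|---|---|
| 2% / 2% | 18.4 |
| 5% / 5% | 19.0 |
| 10% / 10% | 20.0 |
| 2% / 5% | 17.4 |
| 5% / 10% | 17.1 |
| 5% / 2% | 20.0 |
| 10% / 5% | 21.9 |

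Of 150 per arm, 2% and 5% are 3 and 7.5 patients, or 10.5 in all; 5% and 10% are 7.5 and 15, or 22.5 in all.

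**4. Power**

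Losing 2, 5 or 10 points beyond the planned 20% leaves 117, 112.5 or 105 per arm, and power falls from 81.4% to 80.4%, 78.9% or 76.0%.

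**The case against.** The best defence is that section 2.13 is the article's only account of what withdrawal involves. There it means retrieving the drug while endpoint follow-up goes on. On that view, withdrawal under section 2.5 carries the same duties and no event is lost. This is a fair reading, and it is why loss of event follow-up is a risk here and not a stated fact. It does not settle the matter, because section 2.13 is written for patient-decided withdrawal and does not secure the week-12 value.

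Several stronger readings are tempting, and the article does not support them:

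- *Every participant with a serious adverse event is removed.* Unblinding applies only when judged necessary. A reader might multiply an assumed 5–15% event rate by 300 to get 15–45 patients and set this against the planned margin of about 22 responders per arm (0.1802 × 120 = 21.6). That treats each event to week 24 as an unblinding, counts unblinding after week 12, which cannot affect the primary value, and compares a two-arm total with a per-arm figure.
- *Adverse-event follow-up ends.* No section says so. Section 2.8 asks for duration and prognosis to be recorded.
- *Unblinded participants are dropped from the analysis.* Section 2.10 does not exclude them. The strain with intention-to-treat is about collecting the data, not about membership of the analysis set.
- *Missing primary values have no planned handling.* That may be in the analysis plan, which is not shown, so it is no finding.

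It is also true that a patient who dies before week 12 has no NT-proBNP value under any unblinding rule.

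**Conclusion.** The point holds as a conflict between sections and an avoidable risk to the primary outcome. Section 2.5 states a rule that ends study participation, with a named trigger that overlaps the efficacy events. Section 2.13 softens it only in part and for a different group. A participant unblinded before week 12 may lose the only post-baseline NT-proBNP for reasons related to outcome.

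The likely size is modest: about 1.0 to 1.9 points of spurious difference for a 3 to 5 point imbalance, with no true effect. This rests on assumed withdrawal rates, on all withdrawn patients being non-responders, and on a complete-case analysis. At low unblinding rates the effect would be smaller. What justifies acting is the direction, since under these assumptions the arm that loses more such patients looks better, and the fact that uncollected values cannot be recovered later.

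**What to change.** Amend section 2.5 so that unblinding does not end follow-up. Possible wording: *Participants who are unblinded remain in the study, subject to their consent, and complete all scheduled assessments, including NT-proBNP at week 12 and clinical and adverse events to week 24. They are analysed in the arm to which they were randomised, and the unblinding is recorded.*

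Extend section 2.13 to name participants unblinded by the study team, so that the two sections give sites one instruction. When to unblind, and whether study drug continues, are left to the clinical team and are not part of this change.

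The cost is a short amendment, with the ethics approval that section 2.12 requires before any modification, and completion of visits already in Table 2 for what should be a few patients. It should be made before affected participants reach week 12.
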